# Evaluating the Effectiveness of the Motivational Interviewing–Based Wellness Coaching for Kids and Families (WC4K) Program in Pediatric Obesity Care: Protocol for a Cluster Randomized Pragmatic Trial

**DOI:** 10.2196/78792

**Published:** 2026-02-10

**Keywords:** childhood obesity, motivational interviewing, pediatric primary care, pragmatic trial, lifestyle coaching, health equity

## Abstract

**Background:**

The increasing prevalence of severe obesity among youth and the early onset of comorbidities highlight the urgent need for effective solutions to support behavior and lifestyle changes. Motivational interviewing (MI), a client-centered counseling technique, has shown promise in improving obesity-related outcomes and is now recommended by the American Academy of Pediatrics as a key component of behavioral interventions for children with overweight and obesity.

**Objective:**

This study aimed to describe the design and baseline characteristics of the Wellness Coaching for Kids and Families (WC4K) program, an MI-based behavioral health intervention integrated into pediatric primary care within a large integrated health care system. This trial aims to inform broader implementation strategies for other health care systems.

**Methods:**

We are conducting a cluster randomized pragmatic trial across 50 pediatric clinics within Kaiser Permanente Southern California. Clinics were randomized to either the intervention arm (n=24, 48.00%) or the usual care arm (n=26, 52.00%), targeting children aged between 3 and 8 years with overweight or obesity. Pediatricians in intervention clinics received MI training and referred families to centralized health coaches for tailored telephone counseling. Key behavioral targets include increased fruit and vegetable intake, reduced consumption of sugar-sweetened beverages, increased physical activity, and reduced screen time. The primary outcome is a change in BMI-for-age, measured as relative distance from the median using electronic medical record data. Secondary outcomes include parent-reported behavior change indicators.

**Results:**

The source population includes 150,482 children from clinics serving predominantly low-income and racial and ethnic minority populations. After randomization, intervention and control clinics were similar in demographics (standardized mean differences <0.2 for key variables), with 77,481 (51.49%) children in the WC4K intervention clinics and 73,001 (48.51%) children in the control clinics. In the total clinic population, 36.58% (55,052/150,482) of the children were overweight or with obesity. Enrollment started in fall 2022, study results are expected in spring 2027.

**Conclusions:**

If the trial results indicate success in reducing BMI and improving health behaviors, WC4K may offer a scalable and sustainable model for integrating behavioral health coaching into pediatric primary care. By leveraging MI-trained pediatricians and centralized health coaching, WC4K has the potential to facilitate meaningful lifestyle changes in children with overweight or obesity.

**Trial Registration:**

ClinicalTrials.gov NCT05143697; https://clinicaltrials.gov/study/NCT05143697

**International Registered Report Identifier (IRRID):**

DERR1-10.2196/78792

## Introduction

Childhood obesity in the United States has escalated substantially over the past 3 decades, with the prevalence increasing from 10.0% in 1988 to 1994 to 19.3% in 2017 to 2020 among children aged between 2 and 11 years [1]. This trend has immediate consequences, including elevated blood pressure, insulin resistance, and psychosocial issues [2-8] as well as long-term risks, such as type 2 diabetes, cardiovascular disease, and premature mortality [9-14].

With approximately 1 in 5 US children living with obesity by the age of 11 years [1], effective interventions are urgently needed. Despite decades of public health efforts [15], the increasing prevalence of severe obesity and the early onset of obesity-related comorbidities in youth underscore the urgent need for scalable, effective treatments [16-18].

The American Academy of Pediatrics (AAP) now recommends comprehensive, intensive behavioral interventions, with motivational interviewing (MI) identified as a key component of treatment [16]. Traditional counseling approaches often rely on directive advice giving, which may not be the most effective method for promoting sustained behavior change [19]. In contrast, MI is a client-centered, collaborative technique that helps individuals resolve ambivalence and align behavior with personal values [19,20]. Originally developed to treat substance use disorders [21], MI has since demonstrated efficacy across a range of health behaviors, including diet, physical activity, and weight management [16,22-24].

In pediatric populations, MI has shown promise in improving obesity-related outcomes when delivered by trained health care providers [25-29]. Pediatricians are uniquely positioned to address childhood obesity through routine screening, anticipatory guidance, and family-centered counseling [30-33]. Although many express a strong desire to play a more active role in prevention and treatment, pediatricians report feeling underprepared to manage obesity effectively, citing limited training, a lack of confidence in achieving results, or being overwhelmed by other responsibilities [33-36]. More than 80% of the pediatricians report that they are disappointed in their ability to treat childhood obesity [36]. However, when equipped with behaviorally informed tools such as MI, pediatricians can successfully engage families and support meaningful change [37,38].

Qualitative studies have shown that parents often underestimate the long-term impact of early weight gain unless explicitly counseled by their pediatrician [39]. To address these needs, the Wellness Coaching for Kids and Families (WC4K) program was developed to adapt an existing primary care obesity intervention previously tested in the AAP Pediatric Research in Office Settings network for real-world implementation in a large, integrated health system [37,40]. Key features of WC4K include the integration of program components into the electronic medical record (EMR) system, the initiation of lifestyle treatment through pediatricians, centralized MI-trained health coaches, flexible MI dosing, telehealth delivery, and mobile-friendly tools for communication and engagement. This pragmatic trial aims to evaluate the effectiveness of WC4K in routine pediatric care and inform broader implementation strategies.

## Methods

### Study Design

The WC4K trial is a cluster randomized pragmatic trial with a parallel design, evaluating the effectiveness and sustainability of an MI-based behavioral health intervention integrated into pediatric primary care. Clinics were the unit of randomization. This study was guided by the Pragmatic-Explanatory Continuum Indicator Summary tool [41,42], with scores of 4 or 5 across all 9 domains indicating a highly pragmatic approach.

The WC4K program uses MI to promote healthy lifestyle changes aimed at reducing excess weight in children with overweight or obesity. Key behavioral targets include fruit and vegetable intake, consumption of sugar-sweetened beverages, physical activity, and screen time. The intervention is a modified version of the Brief Motivational Interviewing to Reduce BMI (BMI^2^) intervention [40]. This study uses an implementation-effectiveness hybrid design (type 2) to allow a simultaneous evaluation of clinical outcomes and implementation processes [43].

### Ethical Considerations

The Kaiser Permanente Southern California (KPSC)/Hawaii Institutional Review Board approved this study and granted a waiver of informed consent because the study posed minimal risk, involved secondary use of routinely collected clinical data, was embedded into routine clinical care (including wellness coaching), and could not practicably be carried out with individual consent. The study is registered on ClinicalTrials.gov (NCT05143697). Wellness coaching was offered as a covered clinical service; no additional compensation was provided for research participation. All interactions occurred with parents or caregivers; no direct data collection or assent procedures were conducted with children. Study data were derived from KPSC electronic medical records. All data were stored on secure, password-protected servers behind institutional firewalls. Data access was restricted to study personnel, and all analyses were conducted within the health system’s secure computing environment. No individual-level data are publicly available.

### Population

KPSC provides care for more than 4.6 million members, including approximately 900,000 children and adolescents as of January 1, 2025. The membership population is generally reflective of the population in the region [44]. The eligible population includes parents and caregivers of children aged between 3 and 8 years with overweight or obesity who receive care at participating clinics. No exclusion criteria were applied, consistent with the pragmatic nature of the trial.

### Health Care Setting

KPSC operates under a prepaid, integrated care model where physicians are salaried, enabling a focus on evidence-based care rather than service volume [45]. The infrastructure supports coordinated care across primary, specialty, and hospital services, with a strong emphasis on prevention and chronic disease management. Members typically have access to preventive services with minimal out-of-pocket costs. Lifestyle coaching is a covered benefit.

Patient information is captured in EMRs, which support population health management tools, such as electronic referrals, centralized services, and follow-up reminders. These features facilitate rapid implementation of care adaptations across the region.

### Clinic Selection

Of the 88 pediatric clinics in the KPSC region, 50 (56.82%) clinics with the highest proportion of low-income and racial and ethnic minority patients were selected. One clinic served as a pilot site. The 50 clinics were grouped into small (<300 children), medium (300-999 children), and large (≥1000 children) clinics based on their pediatric population at the target age group and block randomized using clinic size, resulting in 24 (48%) clinics in the WC4K intervention arm and 26 (52%) clinics in the usual care arm.

### Recruitment

Recruitment occurred during scheduled well-child visits using routine workflows. Pediatricians used EMR-embedded tools to identify and refer eligible families to coaching (Figure 1). Recruitment concluded in intervention clinics in December 2024. For control clinics, a synthetic control cohort will be created to address potential differences in demographic and clinical characteristics (more details are provided in the Statistical Analysis section).

**Figure 1 figure1:**
[figure not shown]
Study flowchart. KPSC: Kaiser Permanente Southern California.

### Planning and Piloting Phases

#### Overview

One pediatric clinic volunteered to serve as the pilot site. Workflows were developed and vetted with regional leadership to ensure seamless integration into usual care. EMR tools were built during this phase to support pediatrician referrals and family engagement.

The pilot led to a streamlined role for pediatricians, focusing on initiating MI-based referrals rather than delivering extensive counseling. Pediatricians used MI strategies to engage families and refer them to centralized health coaches. Table 1 summarizes the differences in workflow and treatment components between WC4K and usual care, and Figure 2 shows the wellness screener.

**Table 1 table1:** Comparison of lifestyle treatment in Wellness Coaching for Kids and Families (WC4K) program and usual care and the roles of pediatricians and lifestyle coaches.

Roles	WC4K	Usual care
Previsit questionnaires	AAP^a^ Bright Futures–consistent assessment for well-child visits Wellness screener to assess key target behaviors	AAP Bright Futures–consistent assessment for well-child visits
Pediatricians	Initiate discussion about LT^b^ during well-child visits Use key MI^c^ strategies (explore, guide, and choose) to obtain buy-ins for referral to MI-based lifestyle coaching Enter referral to health coaches Provide educational materials and self-monitoring logs to parents	Initiate discussion about LT during well-child visits Usual communication style, mostly directive Enter referral to LT classes or self-study videos Provide educational materials and inform families about KP.org materials
Health behavior and lifestyle treatment mode	MI-based lifestyle coaching Intake appointment (45 min); 5-9 follow-up visits (20 min) over 24 months	Online group class with a trainer or coach: 16 sessions (75 min); abbreviated version available (4×60 min) On-demand self-study videos about a healthy diet and lifestyle (3×20 min)
Target behaviors	Fruits and vegetable intake, exercise, sedentary time, sugar-sweetened beverages, and snack foods, consistent with AAP Bright Futures guidelines	Fruit and vegetable intake, exercise, sedentary time, sugar-sweetened beverages, and snack foods, consistent with AAP Bright Futures guidelines

^a^AAP: American Academy of Pediatrics.

^b^LT: lifestyle treatment.

^c^MI: motivational interviewing.

**Figure 2 figure2:**
[figure not shown]
Wellness screener sent at scheduling of well-child visit (intervention clinics only).

#### Usual Pediatric Care With Attention Control

In control clinics, pediatric care followed standard practices aligned with AAP Bright Futures guidelines [46-48]. Families completed a previsit questionnaire, and pediatricians used responses and Centers for Disease Control and Prevention (CDC) BMI growth charts to guide discussions [49,50]. Pediatricians provided general lifestyle advice and referred families to virtual health behavior and lifestyle treatment classes or self-study videos. As part of usual care, target behaviors for general lifestyle advice are fruit and vegetable intake, sugar-sweetened beverages, and energy-dense foods, promoting at least 60 minutes of daily physical activity and limiting screen time to below 2 hours per day. No MI training was provided in control clinics.

#### Pediatric Care Following the WC4K Program

The WC4K program builds on the BMI^2^ framework and emphasizes MI as its core behavioral strategy [40,51,52]. Pediatricians in intervention clinics received structured MI training, including EMR-integrated tools to support behavior change conversations. Families completed the same previsit questionnaire as in control clinics and a wellness screener to prioritize health behaviors for discussion (agenda setting; Figure 2). Target behaviors are similar to usual care.

During the well-child visits, pediatricians applied MI techniques to engage families. For parents of children identified as being overweight or having obesity, they encouraged participation in the WC4K program and initiated a “warm handoff” by entering a referral to centralized health coaches. Depending on the clinical encounter, pediatricians also provided families with self-monitoring logs and printed educational materials.

#### MI Training and Counseling Approach

MI differs from traditional directive counseling by focusing on eliciting intrinsic motivation. MI emphasizes autonomy, collaboration, and intrinsic motivation. In pediatric care, especially with young children aged between 3 and 8 years, MI is primarily directed toward parents or caregivers, who play a central role in shaping the child’s health behaviors. MI-trained pediatricians and health coaches avoid direct persuasion and instead focus on building high-quality motivation before initiating action planning.

In MI encounters, pediatricians assess and reflect on the patient’s and their family’s routines, values, and goals and encourage families to consider how current behaviors impact their child’s health and development. Ambivalence and resistance are explored respectfully, allowing families to voice their own reasons for and against change. This process helps align behavior change with what matters most to the family, such as supporting their child’s growth, confidence, or long-term well-being.

Key MI techniques include reflective listening and eliciting change talk—statements that express desire, ability, reasons, or a need for change. Reflections can be viewed as a form of hypothesis testing, helping caregivers clarify their thoughts and motivations. MI assumes that individuals are more likely to act on ideas they articulate themselves [53], a concept known as change talk [53-56].

The WC4K program trains pediatricians to use the 3-phase MI model: *explore, guide, and choose* [19,20,40,57,58]. Although this model often follows a temporal sequence, starting with exploring concerns and guiding toward options before choosing a plan, not all encounters follow a linear path. Some patients may arrive ready to act, while others may need more time to build motivation. The flexibility of MI allows pediatricians to tailor conversations to each family’s readiness, cultural context, and emotional state, making it especially valuable in pediatric obesity care.

To support implementation, pediatricians in intervention clinics had access to a study dashboard displaying referral and uptake metrics. For ongoing training, video modules were provided featuring example encounters and demonstrations of MI techniques tailored to pediatric care. The training was eligible for maintenance of certification part 4 credit, with participation actively encouraged by regional leadership.

#### WC4K Lifestyle Coaching

Health coaching was delivered by a centralized team of MI-trained coaches with more than 5 years of experience. Coaching included a 45-minute intake session and 5 to 9 follow-up sessions (approximately 20 min each) over 24 months.

Coaches worked with parents to set goals, track progress, and reinforce behavior change. Children were encouraged to attend the coaching sessions, but participation was optional and dependent on family preferences and logistics.

#### MI Fidelity

To ensure fidelity, coaches participated in ongoing supervision and periodic session reviews using validated fidelity checklists [59]. Pediatricians were offered MI fidelity assessments using standardized patient encounters and could receive up to 3 one-on-one coaching sessions to improve MI skills.

#### Outcome Measures

The primary outcome is a change in BMI-for-age over 24 months, measured as the relative distance from the median using EMR data and CDC extended BMI percentiles [50,60-62]. No additional visits were scheduled for height and weight collection. Secondary outcomes include parent-reported behavior changes.

At KPSC, height and weight are measured by clinical staff during routine care and automatically recorded in the EMR, allowing for real-time BMI calculation (weight in kg divided by height in m^2^).

### Statistical Analysis

#### Identification of the Control Cohort

Children in the control cohort were identified from EMR records based on having a well-child visit during the study period. To construct a comparable control cohort, we will apply inverse probability of treatment weighting using propensity scores to adjust for confounding [63].

Each child’s propensity score (defined as the probability of being referred to WC4K) will be estimated using observed covariates, including age, sex, baseline relative distance from the median BMI-for-age, socioeconomic status, and other EMR-derived factors. Children in control clinics will then be weighted by the inverse of their propensity score, allowing a balanced comparison with the intervention group and reducing selection bias [63].

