#### Power

The power analysis was performed for the primary outcome, the difference in the change in the relative distance to the median BMI-for-age, and takes into account the intraclass correlation among children within clinics [64].

Across the 49 selected medical centers (Figure 1), the number of children aged between 3 and 8 years with overweight or obesity ranged from 500 to 6000 per site, with a coefficient of variation of 0.9. On the basis of previous studies [65,66], we assumed that the participating children would average approximately 30% to 40% above the median (which equates to the 97th percentile; SD 20% to 25%). Based on an expected effect size of 5.3% (SD 14.7%), a Cohen *h* of approximately 0.3 was used.

With 24 clinics in the intervention arm and 26 in the control arm and assuming a 2-sided α of .05, an intraclass correlation of 0.01, a coefficient of variation of 0.9, and an SD of 27.0% for change in BMI distance, a sample size of approximately 3300 children per arm provides adequate power to detect a difference in difference (DID) of 1 to 5 units in the primary outcome.

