#### Planned Statistical Analysis

To evaluate the intervention effect, we will use a DID approach comparing the change in BMI-for-age distance between the WC4K and usual care groups. Using repeated measurement data, the DID model will estimate the average within-child change from baseline to follow-up, using all available BMI data points.

A linear mixed-effects regression model will be used to account for clustering. The model will include a random intercept for “child” to account for repeated measures. Baseline covariates with standardized mean differences (SMDs) greater than 0.1 between groups will be included as fixed effects, along with relevant demographic, clinical, and site-level characteristics.

For descriptive comparisons, SMDs will be used to assess the balance between groups.

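### Control children are to be weighted by 1/(probability of referral), which favours the controls least like the referred children and widens the imbalance it should remove

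*Protocol article*

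**What the plan says.** The point sits in the Protocol article, Statistical Analysis, under Identification of the Control Cohort. The parts that matter are these:

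- Who the controls are: "Children in the control cohort were identified from EMR records based on having a well-child visit during the study period".
- The method named: "we will apply inverse probability of treatment weighting using propensity scores to adjust for confounding".
- The score: it is "defined as the probability of being referred to WC4K", estimated from "age, sex, baseline relative distance from the median BMI-for-age, socioeconomic status, and other EMR-derived factors".
- The weight: "Children in control clinics will then be weighted by the inverse of their propensity score".
- The purpose: "allowing a balanced comparison with the intervention group and reducing selection bias".

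No weight is stated for the referred children. Under Planned Statistical Analysis, the outcome model is a difference-in-difference (DID) mixed model with a random intercept for child, and "Baseline covariates with standardized mean differences (SMDs) greater than 0.1 between groups will be included as fixed effects".

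**The concern.** Write e for the probability of referral given the covariates. The text fixes the control weight at 1/e. In inverse probability of treatment weighting that weight belongs to treated children. Applied to untreated children it favours those with small e, who resemble the referred group least.

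Baseline distance from the median BMI is a named covariate in e and is also the starting value of the primary outcome. If heavier children are referred more often, 1/e pulls the control group's baseline down while the referred group stays high. The DID then compares groups that start far apart, and regression to the mean alone produces a difference in change. That difference looks like benefit.

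**Working it through.** The plan prints no weight, standardized mean difference (SMD) or effective sample size for this step, so there is no stated figure to reproduce. The check is algebra, an exact small example, and an illustration built on the plan's own inputs.

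**1. Direction.** Coherent control weights:

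| Target | Referred | Controls |
|---|---|---|
| Effect in the referred, e fitted on referred plus controls | 1 | e/(1-e) |
| Effect in the referred, e fitted in intervention clinics and carried over | 1 | e |
| Effect in the whole population | 1/e | 1/(1-e) |
| As written | not stated | 1/e |

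The first three control weights increase in e. The stated one decreases.

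**2. Exact example.** Take two strata of 1,000 children, with e = 0.1 (low) and 0.5 (high). Referred: 100 and 500. Not referred: 900 and 500. Share of high-e children:

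- Referred: 500/600 = 83.3%
- Controls, unweighted: 500/1,400 = 35.7%
- Controls, 1/e: 900/0.1 = 9,000 and 500/0.5 = 1,000, so 1,000/10,000 = 10.0%
- Controls, e/(1-e): 900 × 0.1/0.9 = 100 and 500 × 0.5/0.5 = 500, so 500/600 = 83.3%
- Controls, 1/(1-e): 900/0.9 = 1,000 and 500/0.5 = 1,000, so 50.0%, the whole-population mix

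The stated weight moves controls from 35.7% to 10.0% when the referred stand at 83.3%.

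**3. Illustration for baseline BMI distance.**

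Inputs from the document:
- Mean 35 and SD 22.5, the mid-points of 30 to 40 and 20 to 25 (Power).
- 12,685 + 15,496 = 28,181 intervention-clinic children with overweight or obesity (Table 3).
- About 3,300 children per arm (Power).

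Assumptions:
- The referred fraction is 3,300/28,181 = 11.7%.
- Baseline distance is normal.
- Referral is logistic in baseline distance, with odds ratio (OR) 1.5 per SD.

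Numerical integration gives:

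| Group | Baseline mean | SMD against referred |
|---|---|---|
| Referred | 42.9 | – |
| Controls, unweighted | 35.0 | 0.35 |
| Controls, 1/e, e from intervention clinics | 26.8 | 0.72 |
| Controls, 1/e, e from pooled data | 27.6 | 0.68 |
| Controls, e/(1-e), pooled e | 42.9 | 0.00 |

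With OR 1.25 the SMD under 1/e is 0.37 to 0.39 (unweighted 0.20). With OR 2 it is 1.19 to 1.24 (unweighted 0.59). A separate simulation over referral rates of 6% to 50% and log-odds of 0.3 to 0.8 per SD gave the same picture in all 12 scenarios: 1/e multiplied the unweighted SMD by about 1.7 to 2.4, and the weights for the effect in the referred brought it to 0.02 or less in absolute value.

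**4. Effect on the DID, with no true effect.** With equal SDs at both times and correlation ρ, the expected change has slope -(1-ρ) on baseline, so

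spurious DID = -(1-ρ) × (referred mean - control mean).

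The gap is 42.9 - 26.8 = 16.1 under 1/e and 42.9 - 35.0 = 7.9 unweighted.

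| ρ | 1/e | Unweighted |
|---|---|---|
| 0.9 | -1.6 | -0.8 |
| 0.8 | -3.2 | -1.6 |
| 0.28 | -11.6 | -5.7 |

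The value 0.28 comes from the plan's change SD of 27: 27² = 2 × 22.5² × (1-ρ), so 1-ρ = 729/1,012.5 = 0.72. If the SD of 14.7 in the same section is the change SD instead, 1-ρ = 216.1/1,012.5 = 0.21, so ρ = 0.79 and the artefact is about -3.4.

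**5. Yardstick.** The plan speaks of detecting 1 to 5 units. From its inputs (intraclass correlation 0.01, coefficient of variation 0.9, SD 27, 3,300 per arm over 24 and 26 clinics), the design effects 1 + [(0.9² + 1)m - 1] × 0.01 with m = 137.5 and 126.9 are 3.48 and 3.29. The effective sizes are 948 and 1,003. The standard error is 27 × √(1/948 + 1/1,003) = 1.22, and the difference detectable with 80% power is 2.80 × 1.22 = 3.4 units.

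**6. Does the planned covariate adjustment undo it?** In a DID with two time points per child, a time-constant main effect drops out of within-child change. In a simulated weighted DID at ρ = 0.8 the estimate was -3.26 both without and with baseline distance as a main effect. Adding a baseline-by-time interaction brought it to -0.10, but the plan names no such term.

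**The case against.** The strongest defence is that the sentence is shorthand. The method is named correctly just before it, a reference is cited, the aim is balance with the intervention group, and a condensed article may compress what the full analysis plan states properly. That is possible, and it means the text does not prove that inverted weights will be computed. It does not rescue the sentence, which names the group, the score and the operation; an analyst following it would compute 1/e. Even if standard weighting was meant, the reader cannot tell 1/(1-e) from e/(1-e), and these target different effects.

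Several objections to the size have force:

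- The 3,300 is a planned sample size, not a count of referrals, and the OR of 1.5 is assumed.
- The -11.6 depends on choosing the change SD of 27 over 14.7 and should not be taken as the expected bias.
- The sign depends on regression to the mean dominating. If heavier children drifted further from the median, the bias would reverse.
- The plan gives 30 to 40 for participating children, whereas the illustration applies 35 to all eligible children. This is harmless: with the referral rate held fixed, moving the mean shifts every group equally and leaves SMDs and DIDs unchanged.

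It is also fair that an SMD near 0.7 would show up in the planned balance checks. But the stated response, adding the covariate as a fixed effect, does not remove the bias in the two-time-point case. With unequal numbers of measurements per child the cancellation is not exact, but nothing in the plan makes the adjustment a remedy.

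**Conclusion.** The concern holds. As written, the control weight runs in the wrong direction and works against its own stated aim. This follows from the definition of the score and needs no numerical assumption. The widening is certain for the score itself and applies to covariates that move with it; a covariate unrelated to referral need not get worse.

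The size is illustrative. Under the stated assumptions (OR 1.5 per SD, 11.7% referred, no true effect) the baseline SMD roughly doubles, from 0.35 to about 0.7. The primary DID acquires a spurious benefit of about 1.6 to 3.2 units at correlations of 0.9 to 0.8, and more if the correlation is lower. That is the same order as the effect the trial is sized to detect. Because the rule feeds the primary comparison, it must be corrected before the analysis is run.

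**What to change.** Replace the weighting sentence with: 'Referred children receive weight 1. Control children receive weight PS/(1-PS), with the PS fitted on referred plus control children; the target is the effect in the referred.' This matches the plan's intention to weight only the controls towards the intervention group. If a whole-population effect is wanted instead, say so, and use 1/PS for the referred and 1/(1-PS) for the controls.

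Two small additions are worth making in the same place: report post-weighting SMDs with a target below 0.1, and use standard errors that are robust at clinic level.

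The cost is one sentence in the protocol or analysis plan and one line of code. No data change is needed. The weighting is described in the future tense and results are expected in spring 2027, so there is still time.
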